### Recruitment of participants and follow‑up

The data will be extracted from January 1, 2008 to December 31, 2019. A selection period will be defined by the 7 years (January 1, 2008 to December 31, 2014) preceding the index date. It will enable us to identify eligible patients and measure all the variables needed for the calculation of the high dimension propensity score (hdPS). Each participant will be assigned to one of the two study groups on the index date (January 1, 2015), and then followed up to December 31, 2019 (Fig. 1).

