#### Clinical endpoints

The effects of CAD screening (versus no CAD screening) in terms of major adverse cardiac events (the first occurrence of any component of the composite outcome, which comprise acute coronary syndrome, coronary revascularization, hospitalization for heart failure or all-cause death); major cerebrovascular events (the first occurrence either of stroke, hospitalization for TIA, or carotid revascularization); major adverse limb events (the first occurrence of any component of the composite outcome, comprising PAD, ischemic diabetic foot, lower-limb revascularization (angioplasty or surgery) or amputation); and CKD or end-stage kidney disease (ESKD, defined as requirement of any sustained renal replacement therapy or kidney transplantation). Each component of these composite endpoints will also be considered individually. Major cerebrovascular events, major adverse limb events and ESKD will be considered during follow-up among participants without a history of each appropriate condition at baseline. Clinical endpoints will be determined according to ICD-10 and codes of the French classification of medical procedure (CCAM) as presented in Additional file 2: Table S2.

Finally, SCADIAB study will also assess the frequency of routine CAD screening, expressed as the number of examinations performed per individual per year.

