### Statistical analysis plan

The data will be analysed by the biostatistician of the “Clinical Epidemiology Unit” of the University Hospital of Bordeaux (USMR). Analyses will be performed using SAS® software, version 9.4 or later (SAS Institute, Cary, NC, USA, http://www.sas.com) and all tests will be performed at the first-order error risk α = 5%. The flow-chart (CONSORT), as well as the characteristics of patients at inclusion (eligibility criteria, epidemiological, clinical, biological characteristics and treatment use) will be presented. Confounding factors will be taken into account through a hdPS score that will involve around 500 variables, according to the Bross formula [26]. A principal component analysis will then allow us to reduce the dimensionality to 30 components, and the goodness of fit of this hdPS score will be estimated by a graphical comparison of the score distribution and by standardized mean differences between the two study groups [27]. Comparisons between the two groups will be carried out with and without adjustment for the hdPS score, and the hypotheses of the different regression models chosen, will be systematically verified.

Regarding the analysis of the primary endpoint, a gross estimate of the incremental cost per life-year gained at 5 years will be conducted. The confidence interval (CI) of this incremental cost-effectiveness ratio will be estimated by boostrap (5000 iterations). The analysis will be performed as Intent to Treat. To investigate a possible relationship between the frequency of screening and survival, we will define four different subgroups: screening conducted at least once a year, less than once a year (and at least once every two years), less than once every two years (and at least once every three years), and only once during the follow-up period.

A cost-consequence analysis will be performed linking results of all direct costs (observed during the following period) and results on major cardiovascular events. A budget impact analysis will be conducted to determine the public expenses of the spread of a systematic screening for silent ischemic CAD.

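### The frequency-survival analysis, as worded, classifies patients by exams in the follow-up in which their survival is measured, so it builds in immortal-time bias

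*Protocol article*

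**What the plan says.** The Statistical analysis plan section introduces the analysis with "To investigate a possible relationship between the frequency of screening and survival, we will define four different subgroups". The levels are: at least yearly; below yearly but at least every two years; below every two years but at least every three; "and only once during the follow-up period". No window is written for the first three levels.

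The section on recruitment and follow-up separates two periods. On exposure and covariates: "A selection period will be defined by the 7 years (January 1, 2008 to December 31, 2014) preceding the index date". Patients are then assigned on 1 January 2015 "and then followed up to December 31, 2019". The two study groups are defined by exams in the selection period, that is, before survival starts to count.

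The Clinical endpoints section also reports screening frequency, "expressed as the number of examinations performed per individual per year". It does not say whether the years are calendar years or years alive, and it does not link frequency to survival.

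**The concern.** In the main comparison, exposure is complete before follow-up begins. In the frequency analysis, on its own wording, exposure accrues during follow-up. A patient who dies in 2015 has little chance of collecting five exams by the end of 2019, whatever the effect of screening, while someone in the top level has largely had to survive to get there. The exposure level therefore depends on the outcome.

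The stated adjustment cannot repair this. The high-dimension propensity score is built from variables measured before the index date, and the problem is created after it.

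This is the only planned analysis that relates screening interval to an outcome, and its levels resemble the intervals in the sponsor's physician survey in the Background (once a year 42%, every two years 20%, every three years 33%). A spurious gradient could be read as evidence on how often to screen.

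**Working it through.** **1. The plan's own figures.** The article gives no effect size or power for this analysis. Its only size figure reproduces: 2,400,000 × 0.38 × 0.10 = 91,200, consistent with at least 90,000 eligible patients.

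**2. The levels as counts over a fixed five years.** 5/5 = 1 per year, so the top level needs 5 or more exams. Counts of 3 and 4 (0.6 and 0.8 per year) form the second level, 2 (0.4 per year) the third, and 1 the only-once level.

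**3. A world in which screening does nothing.** Assumptions, none from the article: constant death hazard h, independent of exams; exams stop at death; Poisson exam timing; underlying rates of 1, 1/2, 1/3 and 1/10 per year in shares of 30, 20, 25 and 25%. Let p_k(t) be the probability that a person observed for t years has a count in level k. Then:

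- deaths in level k: D_k = ∫₀⁵ h·e^(−ht)·p_k(t) dt
- survivors in level k: S_k = e^(−5h)·p_k(5)
- person-years: T_k = ∫₀⁵ t·h·e^(−ht)·p_k(t) dt + 5·S_k
- apparent five-year mortality: D_k/(D_k + S_k); death rate: D_k/T_k

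With h = 0.04, true five-year mortality is 1 − e^(−0.2) = 18.1% at every level. The apparent values are:

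- At least yearly: D = 0.0101, S = 0.1609, T = 0.844. Mortality 5.9%; rate 1.20 per 100 person-years.
- Second and third levels: mortality 10.8% and 15.0%.
- Only once: D = 0.0423, S = 0.1684, T = 0.948. Mortality 20.1%; rate 4.46 per 100 person-years.

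The death-rate ratio, top level versus only once, is 1.20/4.46 = 0.27, where the truth is 1. The mechanism shows in p_k(t): the chance of being in the top level is 0.1% after one year of observation and 19.7% after five; for the only-once level it is 25.3% and 20.6%.

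**4. Sensitivity to the assumptions.** The table gives the null death-rate ratio, most versus least frequent level. The first two columns use the rate mix above with mortality of 2 to 8% per year. The third uses gamma-distributed exam rates (mean 0.3 to 0.5 per year, shape 0.5 to 2, all assumed) with mortality of 3 to 8% per year.

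| Classification | Poisson timing | Regular timing | Gamma-Poisson |
|---|---|---|---|
| Count over fixed 5 years | 0.27 | 0.06–0.07 | 0.28–0.43 |
| Exams per year alive, one-exam patients kept as only once | 0.66–0.69 | 0.25–0.28 | 0.7–1.1 |
| Exams per year alive, one-exam patients classed by rate | 2.08–2.21 | 1.06–1.21 | 2.2–3.5 |
| Levels from the 7-year selection period | 1.00 | 1.00 | about 1.0 |

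In the third row, regular timing brings the extreme levels close together, but the distortion remains between neighbours: at 4% mortality the second level has 8.25 deaths per 100 person-years against 2.38 in the top level.

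**5. Reading across.** Only the selection-period classification returns the true value under all three exam processes. Everyone who enters follow-up was alive throughout 2008–2014, so the exam count cannot depend on later survival.

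**The case against.** The best defence is that the follow-up window is attached only to the fourth level, while the article otherwise defines screening exposure in the selection period. If the selection period was meant here too, the artefact disappears. The article also states no counting rule or model for this analysis: its Kaplan-Meier curves are by the two study groups, and its Cox models are described in the same context. A full analysis plan may specify time-updated handling.

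The ambiguity stands in part: placing the first three levels in follow-up is an inference. But the four levels form one classification, and the only window written for it is follow-up. That is a stated rule that produces bias, not a detail left out. If something else was meant, the sentence needs correcting anyway.

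A reader might draw four stronger conclusions that the article does not support:

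- *That the choice of denominator alone sets the direction.* The clear reversal needs the article's only-once level to be replaced by a rate band. If that level is kept, a per-year-alive rate gives about 0.7 to 1.1 with gamma-Poisson exams, sometimes close to no distortion.
- *That the main results are compromised.* The primary cost-effectiveness contrast and the clinical endpoints classify patients before the index date.
- *That the two-group propensity score will wrongly be applied to the four levels.* The article does not say which score, if any, this analysis uses. A multinomial score is one option, not a correction of an error.
- *That this drives a listed endpoint.* The article explores a possible relationship; frequency against survival is not among its endpoints.

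**Conclusion.** The concern holds for the frequency-survival analysis as worded. Its exam window and its survival window are the same, and pre-index adjustment cannot undo that. With fixed five-year counts and randomly timed exams, the spurious ratio for at least yearly versus only once is roughly 0.3 to 0.4, and further from 1 if exams are regularly spaced. With exams per year alive, the result depends on the handling of one-exam patients and cannot be predicted from the text. These sizes rest on assumed mortality and exam rates. That exposure depends on survival does not rest on them. The damage is limited to one exploratory analysis.

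**What to change.** In the Statistical analysis plan section, define the frequency levels from exams between 1 January 2008 and 31 December 2014, change the window named for the last level from the follow-up period to the selection period, and relate the levels to survival from 1 January 2015. One boundary then needs attention: two exams in seven years is 2/7 = 0.29 per year, which is below once every three years but is not only once, so the lowest level must be worded to include it.

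If exams during follow-up are wanted, enter a time-updated cumulative exam count in the Cox model. A landmark after two years would not serve these levels: one exam in two years already equals once every two years, so the third level could not be formed.

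The cost is wording and programming, since the planned extraction covers 2008 to 2019. State the downside: frequency then describes past practice, and if the coronary artery disease exclusion applies up to the index date (the article does not give its timing), patients whose earlier screening revealed the disease are not in the cohort.

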### Study groups and methods of CAD screening

#### Screening group

Individuals who had at least one screening exam (stress electrocardiogram test, stress echocardiography, myocardial scintigraphy coupled with stress test or pharmacological stimulation using adenosine, or coronary CT scan) (Table 2) during the selection period (2008–2015).

**Table 2 Tab2:** Codes used to identify tests to screen coronary artery disease

Tests	Procedure codes
Stress test	DKRP004, EQRP002, EQRM001
Myocardial scintigraphy coupled with stress test or pharmacological stimulation using adenosine	DAQL001, DAQL010, DAQL011, DAQL009
Stress echocardiography	DAQM003, DZQM002, DBQM001
Coronary CT scan	ECQH010
Procedure codes: Codes of the French classification of medical procedure (CCAM)	

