Cardiovascular events will be expressed as numbers, cumulative incidence and incidence rates. Kaplan–Meier curves will be elaborated to plot the incidence of endpoints according to study groups (CAD screening versus no screening). Unadjusted comparisons between groups will be done using a log-rank test. Cox proportional hazards regression models will be computed to estimate Hazard ratios, with related 95% CIs, after adjustment for hdPS score.

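### The one propensity score described is built and checked for screened versus unscreened patients, so it is not assured to balance the four screening-frequency levels that are to be related to survival

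*Protocol article*

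**What the plan says.** All passages are in the protocol article.

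- **The score.** The Statistical analysis plan states: "Confounding factors will be taken into account through a hdPS score that will involve around 500 variables". It names no other method of confounding control. The Abstract likewise says that analyses are adjusted for an hdPS, and Strengths and limitations again names hdPS as the answer to confounding.
- **Its exposure.** The study groups are binary. The screened group is "Individuals who had at least one screening exam" in the selection period, and the other group had none.
- **Its check.** Balance is judged by a plot of the score distribution and "by standardized mean differences between the two study groups".
- **Its use.** "Comparisons between the two groups will be carried out with and without adjustment for the hdPS score". For clinical events, "Cox proportional hazards regression models will be computed to estimate Hazard ratios, with related 95% CIs, after adjustment for hdPS score".
- **The frequency analysis.** "To investigate a possible relationship between the frequency of screening and survival, we will define four different subgroups". The levels are at least yearly, less than yearly down to every two years, less than that down to every three years, and "only once during the follow-up period". No model, reference level, trend test or adjustment is given for it.
- **Timing.** Recruitment of participants and follow-up places the measurement of hdPS variables in the selection period, January 1, 2008 to December 31, 2014. Extraction starts on the first of those days. Survival is followed from January 1, 2015.

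**The concern.** A propensity score balances covariates across the exposure it models. Here that exposure is any exam versus none. The frequency analysis compares levels of testing among patients who, for the most part, belong to one side of that contrast. What leads to yearly testing (for example severity, symptoms or specialist follow-up) need not be what leads to a single test in seven years. Where the two sets of drivers differ, the two-group score leaves confounding between the levels. A standardized mean difference between the two arms cannot reveal it.

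The direction is open. If sicker patients are tested more often, frequent testing looks harmful. If better-engaged patients are, it looks protective.

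This is the plan's only dose-response analysis and the one closest to routine, repeated screening. The article expects its results to inform recommendations. In a cohort of this size, a modest residual bias can reach statistical significance.

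**Working it through.** **1. The plan's own figure.** Sample size estimation gives 2.4 million people with type 2 diabetes and no coronary disease, 38% with at least two risk factors, and more than 10% with vascular disease: 2,400,000 × 0.38 × 0.10 = 91,200. This is 1.3% above the stated 90,000, which is therefore reproduced. It sets the size of the simulation and has no other bearing here. The article gives no power, effect size or event count for the frequency analysis.

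**2. Set-up (assumptions unless a source is given).**
- N = 90,000 (article), 5 years of follow-up (article), 20 runs per setting.
- Ever screened: logit P = ln(1.5) × X1, so about half are screened.
- Measured confounder of frequency: C = ρ·X1 + √(1 − ρ²)·X2. Here ρ is the correlation between the drivers of any testing and of frequent testing.
- Frequency among the screened: ln(OR) × C plus logistic noise, cut into four levels. Shares are 42%, 20% and 33% from the physician survey in the Background, and the remaining 100 − 42 − 20 − 33 = 5% is assumed to be the once-only level.
- Death rate: 0.04 × exp(ln(HR) × C) per year, with no effect of frequency.
- Analysis: Poisson rate model among the screened, linear trend over the four levels.

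**3. Rate ratio per level under the null** (share of 20 runs with p < 0.05 in brackets):

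| OR, HR per SD | ρ | Unadjusted | Two-group score | Frequency-level score |
|---|---|---|---|---|
| 1.5, 1.5 | 0 | 1.087 (100%) | 1.087 (100%) | 0.996 (5%) |
| 1.5, 1.5 | 0.5 | 1.085 (100%) | 1.064 (100%) | 0.996 (10%) |
| 1.5, 1.5 | 0.9 | 1.083 (100%) | 1.013 (25%) | 0.996 (15%) |
| 1.5, 1.5 | 1 | 1.083 (100%) | 0.997 (10%) | 0.997 (10%) |
| 1.2, 1.2 | 0 | 1.014 (35%) | 1.014 (35%) | 0.996 (5%) |
| 1.2, 1.2 | 0.5 | 1.013 (30%) | 1.009 (20%) | 0.995 (5%) |
| 1.2, 1.2 | 0.9 | 1.013 (25%) | 0.999 (5%) | 0.996 (5%) |

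Where OR or HR is 1.0 there is no confounding, and all three columns stay at 0.995 to 0.998. Twenty runs fix a rejection rate only roughly, so 5% to 15% is compatible with 5%.

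**4. Highest versus lowest level.** Four levels are three steps apart, so the per-level ratio is cubed. For OR and HR of 1.5 with the two-group score:
- ρ = 0: 1.087³ = 1.28
- ρ = 0.5: 1.064³ = 1.20
- ρ = 0.9: 1.013³ = 1.04
- ρ = 1: 0.997³ = 0.99

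A direct estimate of the same contrast, with log-OR and log-HR of 0.4 per SD, gave 1.26, 1.20, 1.05 and 1.01 at the same four correlations. A frequency-level score gave 1.00 to 1.01 throughout. The two routes agree.

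**5. Which window.** The once-only level is counted during follow-up, which begins when survival begins. If all levels are counted there, exposure is fixed by what happens after time zero, and no baseline score of any kind removes the resulting bias. If exams are counted over the whole selection period instead, no covariates precede the count, because extraction starts on the same day. A frequency-level score is therefore necessary but not sufficient.

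**The case against.** The strongest case against is that this is an omission in a condensed article. The frequency analysis is one sentence, and its model may sit in the full analysis plan. It is neither the primary endpoint nor a listed clinical endpoint. This stands in part: silence on the model is not an error, and a reader might infer that the plan commits to the two-group score for the frequency levels, which the text does not say. What remains is a mismatch in what is stated. The article offers one score as its answer to confounding, ties that score and its diagnostics to two groups, and then plans a four-level comparison. Followed as written, that comparison is either unadjusted or adjusted for a score of a different exposure.

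A reader might also infer that the score cannot control confounding between levels, or that a null relation will look like a trend. Neither is supported. At ρ = 1 the two-group score removes the bias, at 0.9 it removes most of it, and with weak confounding little is there to remove. The direction is not determined by anything in the article.

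Larger figures can be produced. With a log-odds of 0.8 per SD for frequency and a log-HR of 0.4, the two-group score left 1.48. That scenario makes the drivers of any testing and of frequency almost unrelated by construction, and no figure in the article supports it.

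Finally, a separate score does not by itself repair the timing of the exam count. That objection stands in full, and the fix below allows for it.

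**Conclusion.** The point holds in a conditional form. The only hdPS described is specified and checked for screened versus unscreened patients. It is not assured to balance the four frequency levels, and the stated diagnostics would not show if it failed. A null relation between frequency and survival can then appear as a trend in either direction. In the assumed null scenarios the highest-versus-lowest rate ratio under the two-group score was about 1.0 to 1.26, falling as the drivers of any testing and of frequency coincide.

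That range rests on assumed confounder strengths (about 0.4 per SD on both log scales at the upper end), on an assumed 4% yearly death rate, and on about half the cohort being screened. The simulated confounder raises both frequency and risk; one acting in opposite directions would produce a ratio below 1. The matter deserves correction because this is the only dose-response evidence planned, but the primary comparison of the two groups does not depend on it.

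**What to change.** In the Statistical analysis plan section:

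1. State that the frequency-survival analysis uses its own adjustment for frequency level, for example a multinomial hdPS fitted among screened patients and applied as weights or covariates. Do not rely on the two-group score for it.
2. Report standardized mean differences across all four levels, pairwise.
3. Count exams in a window that closes before survival is counted, and take covariates from before that window. Splitting the selection period would do this. As an illustration, 2 years for covariates and 5 for counting use the 7 available. Over 5 years, one exam (0.20 per year), two (0.40), three or four (0.60, 0.80) and five or more (at least 1.0) each fall in exactly one level. Over the full 7 years, two exams (2/7 = 0.29 per year) fall in none.

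The cost is one more score model and one balance table from data the extraction will cover anyway, somewhat wider intervals for small levels, and a shorter window for counting exams. If follow-up counting is kept, the text should say that a baseline score does not remove the bias it brings.

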#### No-screening group

Participants who never experienced a screening exam as described above during the selection period (2008–2015), except resting electrocardiogram.

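### Screening-frequency subgroups are formed from exams during follow-up and then compared on survival over that same follow-up, so the comparison is biased even if screening has no effect

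*Protocol article*

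**What the plan says.** The Statistical analysis plan section states the purpose: "To investigate a possible relationship between the frequency of screening and survival, we will define four different subgroups". The upper two subgroups are "screening conducted at least once a year, less than once a year (and at least once every two years"; the lower two are "less than once every two years (and at least once every three years), and only once during the follow-up period". Under Clinical endpoints, screening frequency is to be expressed as "the number of examinations performed per individual per year". Whether the years are a fixed 5 or the time each patient was alive is not said.

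The dates come from Recruitment of participants and follow-up: "A selection period will be defined by the 7 years (January 1, 2008 to December 31, 2014) preceding the index date". The same section says "Each participant will be assigned to one of the two study groups on the index date (January 1, 2015", with follow-up to 31 December 2019.

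The two group definitions label the selection period differently. The screening group needs at least one exam "during the selection period (2008–2015", and the no-screening group is "Participants who never experienced a screening exam as described above during the selection period (2008–2015". The Abstract uses the same 2008–2015 label while also calling the period 7 years long.

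**The concern.** A subgroup built from exams after the index date cannot be known on the index date. A patient who dies early has little time to be examined, so the length of life helps to decide the subgroup, and the subgroup is then used to explain the length of life. Adjustment for a propensity score measured before the index date does not remove this, because the error lies in how follow-up time is allocated to exposure and not in baseline imbalance.

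The Background reports that surveyed physicians screen every one, two or three years, and the Conclusions say that the findings will guide future recommendations. A gradient of survival across screening frequencies speaks directly to that choice. As planned, a gradient would appear whether or not screening does anything.

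**Working it through.** **The plan's own figure.** The article gives no expected result for the frequency analysis. Its one design figure reproduces from Sample size estimation: 2,400,000 × 0.38 × 0.10 = 91,200, consistent with at least 90,000. In a cohort of that size, chance variation would not hide a distortion of the size found below.

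**Which window do the four categories fit?** Divide the exam count by the window length and compare with 1, 1/2 and 1/3 per year.

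| Exams | 5 years (follow-up) | 7 years (selection period) |
|---|---|---|
| 1 | only once | only once |
| 2 | 2/5 = 0.40, third group | 2/7 = 0.29, no group |
| 3 | 3/5 = 0.60, second group | 3/7 = 0.43, third group |
| 4 | 4/5 = 0.80, second group | 4/7 = 0.57, second group |
| 5 | 5/5 = 1.00, first group | 5/7 = 0.71, second group |

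Over 5 years every count of one or more has exactly one place. Over 7 years a patient with two exams has none. This supports reading the stated follow-up window as intended.

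**One patient, two readings.** Take a patient examined once who dies 0.8 years after the index date. Over a fixed 5 years the patient is in the only-once group (1/5 = 0.2 per year). Over time alive the rate is 1/0.8 = 1.25 per year, so the patient meets the at-least-yearly criterion and has also been examined only once. The placement is driven by the death.

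**Simulation under no effect.** The inputs were:
- Exam rates: 42% yearly, 20% every two years and 33% every three years (physician survey in the Background). The remaining 5% were assumed to have 0.2 exams a year.
- Exams follow a Poisson process, independent of death (assumption).
- Constant mortality of 2, 4 or 6% a year (assumption; the article gives no mortality figure).
- 1,000,000 simulated patients, followed for 5 years. Rate = deaths ÷ person-years.

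At 4% a year the true rate is −ln(0.96) = 4.08 per 100 person-years in every patient. After grouping:

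| Grouping | At least yearly | Lowest group | Ratio |
|---|---|---|---|
| Exams ÷ 5 years | 1.24 per 100 (6.1% die) | 5.52 per 100, only once (24.1% die) | 1.24/5.52 = 0.22 |
| Exams ÷ time alive | 3.69 per 100 (16.8% die) | 1.95 per 100, below 1/3 per year (9.6% die) | 3.69/1.95 = 1.89 |

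Across 2–6% mortality the ratios are 0.22–0.23 and 1.85–1.92. A separate simulation with exam rates averaging 0.5 a year gave, on 5-year counts at 5% mortality, 1.80/5.14 = 0.35, and 0.34–0.35 across 3–8%. Other exam-rate assumptions take the time-alive ratio to about 2.3. The correct ratio is 1.00 throughout.

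**Patients with no subgroup.** One exam since 2008 puts a patient in the screening arm, but none of the four subgroups holds a patient with no exam in 2015–2019. In the 4% simulation 14.8% of patients had no follow-up exam, and 45.1% of them died within 5 years.

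**The arms.** With exposure closed on 31 December 2014, the simulated null ratio is 0.99–1.01. If exams during 2015 were counted, it would be about 0.93–1.00, assuming 40–75% screened before the index date and a 5–30% yearly rate of first screening during 2015.

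**The case against.** - *The analysis is secondary in weight.* It is introduced as looking for a possible relationship. It is not the primary endpoint, and no comparison of outcomes by screening frequency is listed among the secondary endpoints. That stands, and it limits the reach of the point.
- *Model and person-time handling belong in a fuller plan.* Their absence from an article is no fault. But the article does fix the subgroups, and it ties the last of them to follow-up. The objection is to what is fixed.
- *The follow-up wording may be a slip for the selection period.* If so, the bias described here goes, but patients with two exams have no subgroup, so the text still needs repair. The categories fit 5 years and not 7.
- *The direction is not settled.* A reader might infer that patients must survive to count as frequently screened, and that frequent screening will therefore look protective. That holds only for fixed 5-year counts. The per-individual-per-year wording also permits time alive as the denominator, which turns the artefact into harm.
- *The arms.* A reader might infer from the 2008–2015 label that the arms themselves use exams after the index date and that the primary endpoint carries the same bias. The documents do not support this: the recruitment section closes the selection period on 31 December 2014 and assigns groups the next day, and the Abstract calls the period 7 years. The label is most likely loose wording.

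**Conclusion.** The point holds for the frequency analysis. As written, it classifies patients by exams after the index date and compares survival over the same years, which gives a wrong answer when the true effect is nil. The null death-rate ratio for at least yearly versus lowest frequency is about 0.2–0.35 on fixed 5-year counts and about 1.9–2.3 on time alive. These sizes rest on assumed mortality, Poisson exam timing and assumed exam rates, partly from a physician survey, so they are illustrations and not bounds. That the classification is biased does not depend on them; the direction depends on a denominator that the article leaves open. The exclusion of screening-arm patients without a follow-up exam follows from the text alone.

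The main arm comparison, and with it the primary endpoint, is not shown to be affected. The date label is a minor wording inconsistency.

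**What to change.** 1. Define frequency only from exams between 1 January 2008 and 31 December 2014, divided by 7 years for every patient. Add a group for less than once every three years, so that all screened patients are classified. In counts: 7 or more; 4–6; 3; and below 3, with two exams in the added group if the only-once group is kept. Every patient is then classified on the index date, and the null ratio is 1.00 by construction.
2. If frequency during follow-up is wanted, analyse it as a time-dependent exposure, or use a landmark: frequency up to a set date, survival counted only after it. Do not use totals taken at the end of follow-up.
3. Separately, replace the 2008–2015 label in the Abstract, Screening group and No-screening group with the exact dates in the recruitment section.

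The cost is a change of wording and the re-coding of one variable; item 2 adds modest analysis work. The small downside of item 1 is that frequency before the index date does not describe screening during follow-up, which the report should say.
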